## Abstract

**ABSTRACT:**

**Introduction:**

Postoperative radiotherapy in patients with breast cancer with one to three lymph node metastases, particularly within the pT1–2N1M0 cohort with a low clinical risk of local–regional recurrence (LRR), has incited a discourse surrounding personalised treatment strategies. Multigene testing for Recurrence Index (RecurIndex) model capably differentiates patients based on their level of LRR risk. This research aims to validate whether a more aggressive treatment approach can enhance clinical outcomes in N1 patients who possess a clinically low risk of LRR, yet a high RecurIndex-determined risk of LRR. Specifically, this entails postoperative whole breast irradiation combined with regional lymph node irradiation (RNI) following breast-conserving surgery or chest wall irradiation with RNI after mastectomy.

**Methods and analysis:**

The RIGAIN (RecurIndex-Guided postoperative radiotherapy with or without Avoidance of Irradiation of regional Nodes in 1–3 node-positive breast cancer) Study is a multicentre, prospective, randomised, open-label, phase III clinical trial that is being conducted in China. In this study, patients with low clinical LRR risk but high RecurIndex-LRR risk are randomly assigned in a 1:1 ratio to the experimental group or the control group. In the experimental group, RNI is performed and the control group omits RNI. Efficacy and safety analyses will be conducted, enrolling a total of 540 patients (270 per group). The primary endpoint is invasive disease-free survival, and secondary endpoints include any first recurrence, LRR-free survival, distant metastasis-free survival, recurrence-free survival, overall survival, disease-free survival, breast cancer-specific mortality and assessment of patient quality of life. The study began in April 2023 and with a follow-up period of 60 months after the last participant completes radiation therapy.

**Ethics and dissemination:**

The study was approved by the Ethics Committee of Sun Yat-Sen Memorial Hospital, Sun Yat-Sen University (SYSKY-2022-097-02, V.3.1). It adheres to the Helsinki Declaration and Good Clinical Practice. Research findings will be submitted for publication in peer-reviewed journals.

**Trial registration number:**

NCT04069884.

STRENGTHS AND LIMITATIONS OF THIS STUDYThe trial is designed as a multicentre, open-label, randomised controlled, phase III study.Introduced a multigene model to guide precision radiotherapy.This research uses invasive disease-free survival as the primary endpoint.The trial is conducted only in one country (China).

## Introduction

 Patients with one to three axillary lymph node metastases constitute approximately 25–30% of early operable breast cancer cases. Radiotherapy plays a pivotal role in the comprehensive treatment of breast cancer.^1 2^ However, the benefit of postoperative radiotherapy for patients with N1 breast cancer, particularly in terms of survival improvement, remains a topic of substantial debate. Studies conducted in the 1990s such as the Vancouver study, DBCG-82b/82c, and the early meta-analysis by the Early Breast Cancer Trialists’ Collaborative Group (EBCTCG) (including the N1 subgroup) consistently demonstrated that postoperative radiotherapy significantly enhances disease-free survival (DFS) and overall survival (OS) for patients.^3^,^7^ Consequently, N1 becomes a relative indication for postoperative radiotherapy. The 2011/2014 EBCTCG meta-analysis further suggested that postoperative radiotherapy could convert a 1.5% reduction in the 10-year any first recurrence (AFR) rate into a 1% 20-year OS benefit.^8 9^ The MA20 and European Organization for Research and Treatment of Cancer (EORTC) 22922 studies published in 2015,^10 11^ which focused on T1–2N1 patients, especially those with high clinical risk of local–regional recurrence (LRR) and compared postoperative regional lymph node irradiation (RNI) after breast-conserving surgery (BCS) or without RNI, found that more aggressive postoperative RNI for T1–2N1 patients could result in better distant metastases-free survival (DMFS), DFS or breast cancer-specific mortality (BCSM). The Vancouver study’s 20-year long-term follow-up results demonstrated the long-term OS benefit of postoperative radiotherapy in the N1 subgroup. These milestone studies further reinforced the value and recommendation of postoperative radiotherapy for patients with N1 breast cancer, rendering N1 staging a strong relative indication for postoperative radiotherapy and increasing the number of patients actively accepting postoperative radiotherapy. Nevertheless, not all N1 patients will benefit from postoperative radiotherapy. Some real-world retrospective studies reveal limited LRR and/or survival improvement from postoperative radiotherapy, particularly RNI therapy, among certain N1 patients, especially those with relatively low clinical risk. Consequently, the necessity of radiotherapy for clinically low LRR risk N1 patients remains a topic of significant controversy and uncertainty. Clinical practice often presents varying professional recommendations for postoperative radiotherapy in low-risk N1 patients, resulting in the exclusion of a substantial number of patients solely based on traditional clinical and pathological features. However, this omission of RNI could lead to inadequate treatment, with potential implications for tumour recurrence, metastasis and patient survival. Conversely, a uniform approach of postoperative radiotherapy for all clinically low LRR risk N1 patients would inevitably result in overtreatment and expose patients to additional risks such as radiation-induced injury and related complications, thereby impacting their quality of life.^12^,^15^

When considering low-risk patients with N1 breast cancer, then, the primary objective is to identify the actual high-risk patients concealed within the clinically low-risk population and to strategically administer postoperative radiotherapy. This represents one of the essential development directions of early breast cancer ‘precision radiotherapy’ in the future. Achieving individualised and precise radiotherapy depends on the discovery of molecular genetic prediction models that can accurately predict LRR risk in a scientific, reliable and accessible manner. Currently approved multigene detection models abroad include Oncotype DX, MammaPrint and EndoPredict. Oncotype DX is the most representative and extensively used multigene prognostic analysis method, primarily employed to guide early luminal low-risk patients to avoid adjuvant chemotherapy. Oncotype DX is currently more frequently used in the radiotherapy field to identify low-risk elderly N0 breast-conserving patients exempt from postoperative radiotherapy. Although the predictive value in the N1 population has initially demonstrated some clinical significance, contradictions exist between various research findings.^16^,^19^ No prospective high-level evidence for multigene models predicting RNI benefits in N1 patients is currently available. The clinical trial Tailor RT (MA39) conducted by the Canadian Cancer Trials Group primarily investigates whether low-risk recurrence patients can be spared from postoperative radiotherapy or RNI. This is currently the only prospective, randomised controlled, phase III study internationally that uses a multigene predictive model to guide precise radiotherapy for N1 patients. The future research outcomes will primarily be applied to guide the omission of postoperative radiotherapy in clinically low LRR risk and genetically low-risk N1 patients. However, the significance of postoperative radiotherapy for patients with intersecting risks, especially those with clinically low-risk but genetically high-risk profiles, remains uncertain.

Recurrence Index (RecurIndex) is the only risk prediction model developed based on the Chinese population for early-stage breast cancer. Consisting of 18 core genes and 10 immunohistochemical 4 reference genes, it is capable of independently predicting the risk of LRR and distant metastasis.^20^,^24^ Internal validation studies in Taiwan and external validation studies conducted in Singapore, Hong Kong and the Fourth Affiliated Hospital of Hebei Medical University in China have all provided strong evidence of RecurIndex’s predictive efficacy and its value in guiding radiotherapy for N1 patients.^25 26^ Low-risk and high-risk patients identified by RecurIndex-LRR had 5-year LRR rates of 0% and 7%, respectively (p=0.0146). Compared with high-risk RecurIndex-LRR patients who did not receive postoperative radiotherapy, those who underwent postoperative radiotherapy demonstrated significantly improved rates of LRR and recurrence-free survival (RFS), with percentages of 88.8% vs 74.1% (p=0.0071) and 79.4% vs 59.5% (p=0.0019), respectively. These results clearly indicate the significant benefits of postoperative radiotherapy in this patient population. To date, RecurIndex has become widely recognised and clinically implemented around the Asia-Pacific region. It has been incorporated into the ‘Expert Consensus on Multigene Testing for Adjuvant Therapy of Hormone Receptor-Positive, Human Epidermal Growth Factor Receptor 2-Negative Early Breast Cancer’ in China and recommended in the ‘Chinese Society of Clinical Oncology Guidelines for the Diagnosis and Treatment of Breast Cancer 2022’ for guiding precise postoperative radiotherapy in N1 patients. However, further high-level, randomised controlled, phase III clinical trials are needed to validate its clinical applications and expand its usage in the field. The most promising and crucial area for its application lies in guiding precise radiotherapy for patients with N1 breast cancer.

In summary, we have begun conducting a multicentre, prospective, randomised controlled, phase III clinical study of individualised precision radiotherapy for patients with clinically low LRR risk breast cancer with N1 guided by RecurIndex. This study aims to evaluate patients’ local recurrence and distant metastasis risks, primarily investigating whether active postoperative radiotherapy can further improve clinical efficacy in N1 patients with clinically low risk but high RecurIndex-LRR risk. The ultimate goal of this study is to provide high-level clinical evidence and reliable multigene recurrence risk prediction models to help achieve individualised precision radiotherapy for patients with N1 breast cancer.

## Materials and methods

The RIGAIN (RecurIndex-Guided postoperative radiotherapy with or without Avoidance of Irradiation of regional Nodes in 1–3 node-positive breast cancer) Study is a multicentre, prospective, randomised, open-label, phase III clinical trial that is being conducted in China. The overall research process is illustrated in figure 1. This study aims to screen postoperative patients with early-stage breast cancer (pT1–2N1M0) who have completed standard systemic therapy and possess eligible pathological specimens for participation. The inclusion and exclusion criteria are listed in box 1. RecurIndex testing will be performed using postoperative paraffin-embedded tissue sections from the primary lesion. The study is divided into a randomised controlled trial and an observational study based on clinical risk and RecurIndex-LRR risk. Patients with low clinical risk but high RecurIndex-LRR risk will be randomly assigned in a 1:1 ratio to either the experimental group (RNI) or the control group (no RNI), while patients with low clinical risk and low RecurIndex-LRR risk will be included in the observational study. This article primarily focuses on the randomised controlled trial. The study participants will receive the following treatments: experimental group: for patients who underwent BCS, RNI will be performed in combination with whole breast irradiation (WBI)+tumour bed boost irradiation. For patients who underwent mastectomy, chest wall irradiation (CWI) will be administered in combination with RNI. Control group: RNI will be omitted. For patients who underwent BCS, only WBI+tumour bed boost irradiation will be administered. For patients who underwent mastectomy, both RNI and CWI will be omitted. A comparative effectiveness analysis will be conducted. The study commenced in April 2023.

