### Objectives and endpoints

This study aims to evaluate whether adjuvant radiotherapy to the regional lymph nodes after BCS or chest wall plus regional lymph node radiotherapy after total mastectomy can further improve clinical outcomes in N1 patients with low clinical risk but high RecurIndex-LRR risk.

The primary endpoint is invasive disease-free survival (IDFS). Secondary endpoints are AFR, LRR-free survival (LRFS), DMFS, RFS, OS, DFS, BCSM and patient quality of life assessment. The specific definitions can be found in table 1.

**Table 1 T1:** The specific definitions of the study endpoints

IDFS	The time from the day the subject is randomised to the earliest occurrence of invasive cancer local recurrence, distant metastasis or death, but does not include contralateral breast second primary cancer.
AFR	Any ipsilateral chest wall, breast, regional lymph node recurrence or distant metastasis event that occurs during the follow-up period.
LRFS	The time from the day the subject is randomised to the earliest occurrence of ipsilateral chest wall, breast, or regional lymph node recurrence or death.
DMFS	The time from the day the subject is randomised to the earliest occurrence of distant metastasis or death.
RFS	The time from the day the subject is randomised to the earliest occurrence of ipsilateral chest wall, breast, regional lymph node recurrence, distant metastasis or death.
OS	The time from the day the subject is randomised until the patient’s death.
DFS	The time from the day the subject is randomised to the recurrence of the disease or the patient’s death due to disease progression.
BCSM	The time from the day the subject is randomised to death from breast cancer.

AFRany first recurrenceBCSMbreast cancer-specific mortalityDFSdisease-free survivalDMFSdistant metastasis-free survivalIDFSinvasive disease-free survivalLRFSlocal–regional recurrence-free survivalOSoverall survivalRFSrecurrence-free survival

During the screening period and 3 months after the end of treatment, patients in each group fill out the quality of life questionnaire (EORTC Core Quality of Life Questionnaire (EORTC QLQ-C30)), as well as the breast cancer survival quality scale (EORTC Breast Cancer-Specific Quality of Life Questionnaire (EORTC QLQ-BS23)) annually during the follow-up phase (onlinesupplemental files 2  3).

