### Safety assessment indicators

All patients participating in the RIGAIN Study are required to undergo safety assessments, including acute radiation reactions and late radiation injuries for radiotherapy patients. The evaluation criteria and handling of injuries are detailed in onlinesupplemental files 4^7^. Their treatment is shown in online supplemental file 8, including acute skin reactions to radiotherapy, symptomatic radiation pneumonitis, long-term cosmetic outcomes (BCS/reconstruction patients), skin fibrosis (total mastectomy patients), ischaemic heart disease, upper limb oedema,^27 28^ brachial plexus injury and second primary tumour.^29^

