#### Follow-up evaluation and toxicity assessment

The registration timeline, intervention measures and assessments are presented in online supplemental file 13. In the follow-up phase after radiotherapy, check-ups and assessments will be performed every 6 months until the occurrence of an endpoint event or the end of the study. For patients without postoperative radiotherapy, check-ups and assessments will be conducted every 6 months after the completion of adjuvant chemotherapy until the occurrence of an endpoint event or the end of the study. Effectiveness evaluations include tumour imaging examinations and assessments, brain MRI or CT, bone scans, quality of life questionnaires (EORTC QLQ-C30) and breast cancer-specific quality of life scales (EORTC QLQ-BS23). Safety evaluations include but are not limited to physical examinations, Eastern Cooperative Oncology Group Performance Status (ECOG PS) scores, pregnancy test checks, blood routine tests, blood biochemistry tests, AEs and serious AEs (SAEs). At the end of the study, participants will undergo physical examinations, performance status assessments (ECOG PS), blood routine tests, blood biochemistry tests, tumour markers, breast ultrasound/MRI, mammography, chest X-ray/CT, abdominal ultrasound/CT, and EORTC QLQ-C30 and EORTC QLQ-BS23 scoring. Evaluations of concomitant medications and AEs are also required. The end-of-study visit window is 60 months after the last participant completes radiotherapy. For participants who are withdrawn or drop out before the end of the study, safety and effectiveness assessments will be conducted according to the requirements of end-of-study safety and effectiveness visits.

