### Statistical analysis

Descriptive statistical analyses will be conducted based on demographic characteristics such as age, gender, height, weight and other baseline characteristics such as medical history. The Cox proportional hazards model will be used for analysis of the primary endpoint. The HR and its 95% CI will be calculated, including stratification factors and other covariates. Additionally, the Cox proportional hazards model without covariates will be used to support the analysis results of the primary endpoint. Moreover, the Kaplan-Meier (KM) method will be used to calculate the median IDFS for the two groups (experimental group vs control group), including 95% CIs. KM plots will be used to illustrate the time trends of IDFS. For the secondary endpoints, the AFR of each group will be calculated, as well as the corresponding 95% Clopper-Pearson CIs. LRFS, DMFS, RFS, OS, DFS and BCSM will be analysed for median values using the KM method (including 95% CIs). The overall changes in EORTC QLQ-C30 and EORTC QLQ-BS23 scores from baseline will be summarised. Safety analysis will be conducted by summarising AEs, changes in laboratory test results, changes in vital signs and study treatment exposure. The results will be reported by treatment group. All AEs during treatment, grade 3 or higher treatment-emergent AEs (TEAEs), SAEs, radiotherapy-related SAEs and TEAEs leading to study termination will be summarised by organ system, preferred term, and group in terms of numbers and percentages (see online supplemental file 16 for details). A p value of ≤0.05 in a two-tailed test will be considered statistically significant. Statistical analyses will be performed using SPSS V.25.0 and STATA V.14.

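### In the mastectomy stratum, visits, the post-treatment quality-of-life form and the adverse-event window are tied to radiotherapy that controls do not receive, so the arms are not on one calendar

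*Protocol article*

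**What the plan says.** Treatment by arm and surgery is set out in Materials and methods. After mastectomy, in the experimental arm: "For patients who underwent mastectomy, chest wall irradiation (CWI) will be administered in combination with RNI". In the control arm: "For patients who underwent mastectomy, both RNI and CWI will be omitted". After breast-conserving surgery (BCS) both arms receive whole breast irradiation and boost; of the controls the article says: "For patients who underwent BCS, only WBI+tumour bed boost irradiation will be administered".

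The section on follow-up evaluation and toxicity assessment starts 6-monthly visits after radiotherapy for irradiated patients. For the others: "For patients without postoperative radiotherapy, check-ups and assessments will be conducted every 6 months after the completion of adjuvant chemotherapy". Table 1 counts IDFS from randomisation for everyone.

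Two further items are tied to treatment. The Statistical analysis section summarises "All AEs during treatment, grade 3 or higher treatment-emergent AEs (TEAEs") together with SAEs and radiotherapy-related SAEs, by group. Objectives and endpoints has patients in each group complete quality-of-life forms at screening, 3 months after treatment ends, and annually in follow-up.

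Safety assessment indicators requires safety assessment of every patient, "including acute radiation reactions and late radiation injuries for radiotherapy patients".

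The abstract labels the contrast briefly: "In the experimental group, RNI is performed and the control group omits RNI". The objective is fuller. Besides nodal irradiation after BCS, it asks whether "chest wall plus regional lymph node radiotherapy after total mastectomy can further improve clinical outcomes in N1 patients".

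**The concern.** A time-to-event endpoint that is partly found at scheduled visits should be looked for on the same calendar in both arms, counted from the same origin as the endpoint. Here the origin is randomisation, but the visit clock depends on whether radiotherapy was given. After mastectomy that is the same as depending on the arm. In an open-label trial with 6-monthly assessments, an arm-dependent clock can make equal risks look unequal when IDFS is read off at a fixed time such as 5 years.

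The same wording affects safety and quality of life. A window that opens and closes with treatment, or a form due 3 months after it ends, has no stated meaning for a patient whose allocated strategy contains no radiotherapy. The tolerability cost of the added radiotherapy is then compared over periods that do not match.

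**Working it through.** **1. Who is affected.**

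| Surgery | Experimental | Control | Visit clock |
|---|---|---|---|
| BCS | Whole breast + boost + nodal | Whole breast + boost | End of radiotherapy in both arms |
| Mastectomy | Chest wall + nodal | None | End of radiotherapy vs end of chemotherapy |

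The clock differs by arm in the mastectomy row only.

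**2. Size of the offset.** Radiotherapy starts 0 to 8 weeks after chemotherapy (General consideration). It lasts 25 fractions at 5 per week = 5 weeks, or 15–16 fractions, about 3 weeks if also given 5 per week (an assumption; Dose prescription and fractionation).
- Shortest: 0 + 3 = 3 weeks.
- Longest: 8 + 5 = 13 weeks, about 3 months, within a 26-week visit interval.

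**3. The plan's own figures.** Five-year IDFS is assumed to be 89% vs 82%. HR = ln(0.89)/ln(0.82) = 0.587, as stated. Under exponential survival the yearly hazards are −ln(0.82)/5 = 0.0397 and −ln(0.89)/5 = 0.0233.

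**4. Shift in 5-year IDFS under equal true risk.** Assumed calendar: controls seen at months 5, 11, …, 53, 59 after randomisation; irradiated patients 3 months later, at 8, 14, …, 56, 62. All events are found at visits. The apparent event-free proportion at month t is exp(−hazard × last visit/12).

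| Read at | Hazard | Control (last visit) | Irradiated (last visit) | Irradiated minus control |
|---|---|---|---|---|
| Month 60 | 0.0397 | 0.823 (59) | 0.831 (56) | +0.8 points |
| Month 60 | 0.0233 | 0.892 (59) | 0.897 (56) | +0.5 points |
| Month 58 | 0.0397 | 0.839 (53) | 0.831 (56) | −0.8 points |

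A simulation of 400,000 patients per arm on this calendar agrees at 5 years: 0.824 vs 0.831 and 0.892 vs 0.897, with a rate ratio of 1.00–1.01. The direction depends on the reading time. With a 3-month offset, controls were seen 3 months more recently during half of each 6-month cycle and 3 months less recently during the other half. A different calendar would give a different gap, of either sign.

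**5. Effect on the primary hazard ratio.** Cox models were fitted to simulated data with offsets of 3 or 13 weeks, a mastectomy share of 50% or 100%, and a true HR of 1.0 or 0.587. Assumptions: randomisation at the end of chemotherapy, exponential events found at the next visit, 12 replicates of 8,000 patients per setting. The ratio of the visit-detected HR to the true-time HR ran from 0.992 to 1.004, a change of less than 1%.

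**6. Dilution in the whole trial.** The mastectomy share is not given. If it were 50%, the month-60 shift over all patients would be 0.5 × (0.5 to 0.8) = about 0.25 to 0.4 points, against a target difference of 7.

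**7. Quality-of-life form.** If the end of treatment is read as the end of chemotherapy for mastectomy controls, their form falls 3 months after chemotherapy. That of irradiated mastectomy patients falls 3 months plus 3 to 13 weeks after it. If it is read as the end of radiotherapy, these controls have no such time point. The article does not say which applies.

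**The case against.** The strongest reply is that this hardly touches the primary result. The analysis is a Cox model from randomisation, the visit interval is 6 months for everyone, BCS patients share one clock, and the article plans no between-arm test at a fixed time. Deaths, and recurrences that present between visits, do not wait for a visit, so step 4 overstates the shift on that calendar. All of this stands, and it is why the point is small.

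It can also be said that the supplements on the assessment schedule and on the analysis may define the treatment period for unirradiated patients. They may, and they are not shown. The visit rule, however, is stated in the article itself, and it differs by arm after mastectomy.

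A reader might infer more than the article supports:

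- **That a chest-wall effect would be passed off as a nodal effect.** The abstract's introduction, the objective and the Discussion all name both parts of the strategy, and randomisation is stratified by surgery. Pooling a declared strategy is legitimate. Hazard ratios by surgery and an interaction test can be left to an analysis plan that is not shown. Only the short label is loose.
- **That controls have no rate for late harms.** Safety assessment is required of all patients, the listed items include arm oedema, ischaemic heart disease and second tumours, and Data management requires all AEs and SAEs to be recorded. BCS controls are themselves irradiated.
- **That on-treatment adverse events in mastectomy controls are zero by construction.** The article leaves their treatment period undefined, which does not make it empty.
- **That the clock always favours the experimental arm.** Month 58 shows the reverse.

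**Conclusion.** The point holds in a limited form. Within the mastectomy stratum the assessment calendar differs by arm by about 3 to 13 weeks, while IDFS runs from randomisation. The pooled hazard ratio moves by less than 1%. A reading of 5-year IDFS in that stratum could shift by about 0.5 to 0.8 points, assuming a near-maximal offset, exponential events and detection only at visits, with a sign that depends on when the curve is read.

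The more practical consequence is for safety and quality of life. As worded, the adverse-event summary and the post-treatment questionnaire do not give mastectomy controls a window matching that of their irradiated counterparts. The documents do not show a biased primary analysis, missing control safety data, or a mislabelled objective.

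**What to change.** 1. Time follow-up visits, quality-of-life forms and adverse-event reporting windows from randomisation, on one calendar in both arms and both surgical strata. Extra on-treatment toxicity checks for irradiated patients can stay as an addition, reported separately.
2. Over that common window, report upper limb oedema, ischaemic heart disease, pneumonitis and second primary tumour by arm for all randomised patients.
3. Let the short description of the arms follow the objective: nodal irradiation after BCS, and chest wall plus nodal irradiation after mastectomy, each against its stated control.

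The cost is a change to the visit-calendar wording and a few tables. Patients without radiotherapy already attend every 6 months and adverse events are already recorded for everyone. Treatment, sample size and the primary test do not change. Enrolment is planned to January 2028, so the calendar can still be aligned for patients yet to enter; for those already randomised, visits can be analysed by actual time since randomisation.
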